### Qualitative data analysis and presentation

Anonymised interview transcripts will be imported into QSR NVivo software platform for thematic analysis.^45^ The analysis will be performed collaboratively between researchers to encourage a breadth and depth of analysis from different perspectives and viewpoints. Initially, the researchers will collaborate to develop a preliminary coding framework. Data coding will be performed by the researchers separately, using an iterative inductive approach^45^ across all qualitative data. In summary, the researchers will broadly follow the steps outlined by Braun and Clarke,^45^ including going through a process of familiarisation with the data by reading and rereading transcripts while making reflective notes on the literal content, looking closely at words used by participants, interpreting what the data meant by assigning initial codes or classifications to segments of text, and exploring relationships between these classifications and developing core themes. Results from qualitative data analysis will be presented in narrative form based on key themes established during the analysis, supplemented by participants’ quotations.

### Adverse events

For the purposes of this work, an adverse event is defined as any unfavourable or unintended sign or response associated with participating in the PR programme of this trial. Due to anticipated thorough participant assessment (including risk assessment) and individualised nature of PR in this trial, adverse events are not anticipated. However, if such events do occur, the programme will be stopped immediately for the affected participant so that they can be given appropriate management, which may include referral to the medical team. All adverse events will be registered on the adverse event log and CRF. Serious adverse events will be reported to the Clinical Research Support Unit at Malawi-Liverpool-Wellcome Trust Clinical Research Programme, College of Medicine Research and Ethics Committee (COMREC), and University of Leicester Research Ethics Committee, for guidance where required.

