Demographic variables including age, sex, ethnic group, highest education level and employment status.Lung health variables including potential risk factors for lung disease (these will be assessed by adapting IMPALA questionnaires^28^ available at https://github.com/jipp3r/IMPALA_QuestionSet, for example, smoking status (pack years) and biomass fuel exposure), primary respiratory diagnosis, time since diagnosis in years, number of CRD exacerbations and hospitalisations within the last 12 months, spirometric measurements (prebronchodilator and postbronchodilator forced expiratory volume in one second (FEV_1_), forced vital capacity (FVC) and FEV_1_/FVC ratio); comorbidities and treatments.Anthropometric measurements of height (using a Holtain stadiometer), weight (using calibrated weight scale) and body mass index (BMI).Health status variables including participants’ perceived respiratory disability due to dyspnoea (using the mMRC dyspnoea scale^29^), health-related quality of life (using the COPD Assessment Test^30^), subjective experience of fatigue (using the Checklist Individual Strength fatigue subscale^31^) and psychological well-being (using the Hospital Anxiety and Depression Scale^32^)—these tools will be translated and administered to participants in a standard manner in Chichewa, with the caveat being that they have not been cross-culturally validated in Malawi.Physical fitness variables including exercise tolerance (using the Incremental Shuttle Walk Test^33^), with before-test and after-test measurements of oxygen saturation (SpO_2_) and heart rate (using a pulse oximeter), blood pressure if not recently documented in the participant’s medical file (using a sphygmomanometer), Borg rating of breathlessness^34^ and Borg rate of perceived exertion.^34^ We will also assess lower extremity muscular strength (using five-repetition sit-to-stand test^35^) and hamstring flexibility (using the chair sit and reach test^36^).

Using combination of researcher observation, interaction with the participants, field notes and informal interviews, we will also assess the feasibility of running the PR programme in this study in the following areas: participants’ recruitment (ie, availability of eligible participants and their referral to our PR programme); retention (ie, number and reasons of participant dropouts); engagement (ie, participants’ enthusiasm with the intervention); and protocol adherence to the exercise regimen at both home and hospital.

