### Intervention description

Interview data from phase 1 will be used to culturally adapt the PR programme. We initially propose a 6-week, twice-weekly, supervised centre-based PR programme, with an additional weekly home-based non-supervised session. The programme will be delivered in a group format and will consist of about an hour of exercise training and another hour of health education. The PR sessions or classes will be run in the Physiotherapy Department at QECH. Participants will be provided with refreshments (ie, during rest periods of exercise sessions) and reimbursed for transport at rates mandated by the local research ethics committee. The initial intensity of the exercise regime will be tailored to each participant’s exercise capacity (ie, using Incremental Shuttle Walk Test performance results for individual participant, that is, 50%–75% of their peak speed achieved on the Incremental Shuttle Walk Test^37^), and gradually increased according to each patient’s improvement over the course of PR (eg, as they are able to do more repetitions of an exercise than they were on the previous session).^38^

At each session, participants will complete a set of exercises designed to improve aerobic fitness, muscle strength, endurance and flexibility. Established principles of exercise training will be used during exercise prescription.^39^ Each participant will also be given an information sheet containing illustrations and instructions written in Chichewa for their weekly home-based exercise session. Participants will be requested to keep a standardised exercise and physical activity diary at home, which will have been pilot-tested a priori. The PR programme will not interfere with the participants’ routine medical care from the primary care and/or referring teams.

The education component will be delivered to participants and their families or caregivers, which address: patients as active participants in their healthcare; understanding of the physical and psychological changes that occur with chronic illness, and coping strategies for these.^40^ Education will be delivered either in group or individual sessions depending on the sensitivity of the topic and insights from phase 1. Table 1 below lists some of the topics that may be covered.^41^

**Table 1 T1:** Education topics

Topics that may be suitable for group sessions	Topics that may require individual consultation

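### The adverse event definition covers only events associated with the rehabilitation programme, so an event thought unrelated need not be logged or, if serious, reported

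*Protocol article*

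**What the plan says.** The Adverse events section of the protocol article fixes the definition for the whole study: "an adverse event is defined as any unfavourable or unintended sign or response associated with participating in the PR programme". Three rules then use the term.

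- **Recording:** "All adverse events will be registered on the adverse event log and CRF".
- **Serious events:** "Serious adverse events will be reported to the Clinical Research Support Unit", and also to the Malawi and Leicester ethics committees.
- **Stopping:** if an event occurs, "the programme will be stopped immediately for the affected participant so that they can be given appropriate management".

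The section also says that no such events are expected, because participants are thoroughly assessed and the exercise is individualised. It gives no separate definition of a serious event and does not say that events count whether or not they are related.

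Other sections describe sources that might pick up illness or injury during the programme. Under Data collection (Phase 2), retention is tracked through the "number and reasons of participant dropouts", and feasibility more broadly through "researcher observation, interaction with the participants, field notes and informal interviews". Under Intervention description, "Participants will be requested to keep a standardised exercise and physical activity diary at home". The Phase 3 text invites completers and non-completers alike to an interview.

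**The concern.** Association with the programme is a condition for being an adverse event at all. Someone must therefore form a view on it before anything is written down. If that view is that the event has nothing to do with rehabilitation, the recording and reporting rules do not apply.

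The judgement is hard to make at the time. These are patients with functionally limiting respiratory disease who are starting an exercise programme, and there is no control group. An exacerbation or admission between sessions could be the disease, the exercise, or both. The safer order is to record first and judge relatedness afterwards, so that others can check the judgement.

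What is at stake is the completeness of the safety record and of serious event reporting. The study is meant to inform a multi-centre randomised trial, so its account of harms will be read beyond these ten patients.

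**Working it through.** The point concerns the wording of a definition. There is no figure in the article to reproduce, so the check is a reading of the relevant text.

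1. **Does one definition govern every safety rule?** Yes. The recording and serious-event sentences use the defined term, and the stopping sentence refers back to it. None introduces a broader class of event.

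2. **Does the text settle what association means?** Not expressly. It could mean caused by the programme, or merely arising while taking part. Two features of the same section favour the causal reading:
   - It expects no adverse events because of assessment and tailoring. That is plausible for harm caused by the exercise. It is not plausible for all illness in patients with a breathlessness score of at least 2 on the modified Medical Research Council scale. Elsewhere the article itself allows for illness: the education topics include managing exacerbations, and Phase 3 interviews may be held at home when illness prevents travel.
   - It stops the programme at once for any adverse event. That suits harm from exercise but not every passing complaint.

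3. **What follows on that reading?** Take an admission between sessions that staff attribute to the underlying disease. It is not an adverse event as defined, so the log and case report form rule does not require an entry. It cannot then be a serious adverse event, so the duty to inform the support unit and the two committees does not arise.

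4. **Does another route fill the gap?** Only in part.
   - Dropout reasons cover events that end participation, not those after which the patient returns.
   - Observation, field notes and informal interviews are described as ways to judge recruitment, retention, engagement and adherence.
   - The home diary is for exercise and physical activity.
   - The post-trial interviews concern acceptability.
   - The "number of CRD exacerbations and hospitalisations within the last 12 months" is listed among the lung health variables on the case report form. It looks back over a year and is not an on-trial event record.

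   Each of these may note an event. None is described as an all-cause event record, and none leads to serious event reporting.

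5. **How many events are affected?** The article gives neither an event rate nor the share of events that staff would think unrelated, so no count can be derived.

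**The case against.** The strongest reply is that the wording is ambiguous rather than exclusionary. It does not say caused by, and it prescribes no relatedness test before logging. Staff who read association as arising during participation would record everything. That is fair as far as it goes, but a definition that leaves this open still permits under-recording, and the rest of the section points to the narrower reading.

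A second reply is that little would go wholly unseen. Patients are to attend twice a week in groups of five, so an admission or marked exacerbation would probably show up as a missed session or a dropout. This reply stands against one tempting inference, that an event left off the log could never be reviewed later. The documents do not support that, because other notes may hold it. The reply does not restore the reporting duty for a serious event.

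Third, the article is condensed, and the case report form and event log are not shown. A reader might infer that exacerbations and admissions will not be asked about in Phase 3, because the repeat assessments named there do not include them. That omission may be condensation only, and nothing here rests on it. The definition is different: the article states it outright and does not leave it to another document.

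Finally, harms are not among the three stated objectives, and the intervention is supervised exercise and education. That limits the weight of the point but does not justify a narrower duty to report serious events.

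**Conclusion.** The concern holds in a limited form. As defined, and on the natural causal reading, an event thought unrelated need not be logged or, if serious, reported. Informal sources may catch some of these events without making them part of safety reporting.

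The effect is confined to safety recording and serious event reporting in ten patients. The feasibility findings and the pre–post clinical comparisons are unaffected. The number of events lost is unknown. A reader might multiply the programme's person-time by an assumed exacerbation rate, but that would count all exacerbations, not those left unrecorded, and the article supplies no rate.

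The conclusion rests on two assumptions: that association is read as causal, and that the full protocol does not override the stated definition. It is worth correcting because the remedy is cheap, but it does not threaten the study.

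**What to change.** Make three changes to the definition and reporting rules, and one to the stop rule.

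- Define an adverse event as any untoward medical occurrence from consent to the final assessment, regardless of presumed cause.
- Record relatedness to the programme as a separate judgement, made after the event has been logged.
- Apply serious event reporting to all serious events.
- Keep the immediate stop for events that are programme-related or make exercise unsafe. Without this, the wider definition would halt rehabilitation for trivial unrelated complaints, because the present rule stops the programme for any adverse event.

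The cost is some rewording and one extra recorded judgement per event. The downside is a few more log entries and a higher recorded event count, part of it unrelated to the programme. The separate relatedness judgement lets readers see that part for what it is.

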## Ethics and dissemination of the results

Ethical approval for this trial was obtained from University of Malawi COMREC, Blantyre, Malawi (protocol number: P.07/19/2752), and University of Leicester Research Ethics Committee, Leicester, United Kingdom (ethics reference: 31574). The results of the trial will be disseminated through oral presentations at local and international scientific conferences or seminars and publication in a peer-reviewed journal. We will also engage the participants who complete the PR trial and the Science Communication Department at Malawi-Liverpool-Wellcome Trust Clinical Research Programme to organise community outreach activities within Blantyre to educate communities about CRDs and PR. We will also broadcast our trial results through national radio station programmes such as the weekly ‘Thanzi la Onse’ (Health of All) programme by Times Radio Malawi. We will formally present our trial results to Blantyre District Health Office and Malawi Ministry of Health.
